### Primary outcome measurement

The NPQ has been widely used in research and has been shown to have high validity and reliability for neck pain measurement [19, 20]. It comprises nine items on the degree and duration of pain, symptoms including numbness, sleep, social activities, and quality of life. The highest score is 100 and high scores indicate severe damage due to neck pain. The efficacy is measured as the percentage improvement in the NPQ. If the efficacy is greater than 30%, the treatment is considered to be successful. The NPQ efficacy rate is the percentage of participants for whom treatment was successful. It will be assessed using repeated longitudinal analysis per group.

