Data normality will be tested through visual inspection of histograms. According to the results of the homogeneity and normality analysis, parametric statistics (Tukey test) or non-parametric statistics (Wilcoxon rank sum test) will be used for the within- and between-group analyses. Descriptive statistics will be used to compare demographic and baseline information and to evaluate the credibility of the groups. If an adjustment for possible baseline incomparability is needed, a covariance analysis will be performed. Efficacy is measured at five time points. Therefore, a repeated measures analysis of variance will be used to investigate the effect of treatment, time, and interaction terms between treatment groups versus time. Two-sided paired *t* tests will use within-group comparisons (comparing baseline to follow-up). A chi-squared test or a Fisher’s exact test will be performed to determine categorical variables between groups and adverse effects, which will be recorded and described as a frequency and percentage. Fisher’s exact test will be used if a cell has an expected value of less than 5 that is equal to or more than 20%. All statistical analyses will be performed with the Statistical Package for Social Sciences (SPSS, version 21.0, SPSS Inc., Chicago, IL, USA) by statisticians who are independent of the research team and blinded to the group allocation. The confidence interval will be established at 95%, and the significance level at 0.05.

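### For the continuous scores, the look of the data chooses between a mean test and a rank test, beside an unconditional ANOVA and paired t tests, and the plan does not say which governs

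*Protocol article*

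**What the plan says.** All of the following comes from the protocol article, under Statistical analyses unless another section is named.

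- **The gate.** "Data normality will be tested through visual inspection of histograms". The next sentence reads: "According to the results of the homogeneity and normality analysis, parametric statistics (Tukey test) or non-parametric statistics (Wilcoxon rank sum test) will be used". Its scope is both kinds of comparison: the chosen test "will be used for the within- and between-group analyses".
- **The longitudinal analysis.** Because efficacy is measured at several time points, "a repeated measures analysis of variance will be used to investigate the effect of treatment, time, and interaction terms between treatment groups versus time". No distributional condition is attached. The outcome sections likewise assign a repeated longitudinal analysis to NPQ, VAS, NDI and SF-36, and the Abstract names repeated measures ANOVA.
- **Within-group change.** "Two-sided paired *t* tests will use within-group comparisons (comparing baseline to follow-up)". Again no condition is attached.
- **Categorical outcomes.** "A chi-squared test or a Fisher’s exact test will be performed to determine categorical variables between groups and adverse effects", with Fisher's test chosen by expected cell counts.
- **The primary outcome.** The Abstract gives it as change in the NPQ. Primary outcome measurement also defines success as more than 30% improvement: "The NPQ efficacy rate is the percentage of participants for whom treatment was successful", and adds, "It will be assessed using repeated longitudinal analysis per group".
- **Blinding.** The statisticians are independent of the research team and blinded to allocation.

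**The concern.** The two branches of the gate are not two versions of one test. One asks whether the arms have the same mean score. The other asks whether values in one arm tend to rank above those in the other, and its p-value is calibrated on identical distributions. Letting the look of the data choose between them means that the question answered can differ from one scale to the next.

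The gate also collides with the rest of its own section. If a score fails the look, the text calls for the rank sum test and still calls for a mean-based repeated measures ANOVA on the same score. Within groups there are again two rules: the gated pair of tests and the paired t test. The rank sum test is for independent samples, so it is the wrong tool for comparing a patient's follow-up with that patient's own baseline.

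What is at stake is the meaning of a reported significant difference in a continuous score. It could reflect a difference in spread or shape and be read as less pain or disability on average. On the Abstract's definition (NPQ change), the primary comparison is one of these scores.

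**Working it through.** **1. The plan's own figure.** Inputs from Sample size calculation: efficacy rates 0.95 and 0.85, significance level 0.05 (taken as two-sided), power 0.80, dropout 10%.

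n per arm = [1.960·√(2·0.90·0.10) + 0.842·√(0.95·0.05 + 0.85·0.15)]² / 0.10² = (0.8315 + 0.3521)² / 0.01 ≈ 140.1

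With continuity correction: (140.1/4)·[1 + √(1 + 4/(140.1·0.10))]² ≈ 159.5, so 160 per arm and 320 in total. Then 320/0.90 = 355.6, so 356. Both stated figures reproduce. They rest on two proportions, so the Tukey/Wilcoxon choice does not enter. The 160 per arm is used below.

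**2. Which rule applies to what.**

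| Data | Gated rule | Unconditional rule in the same section |
|---|---|---|
| Continuous scores, between arms | Tukey or rank sum | Repeated measures ANOVA |
| Continuous scores, within arm | Tukey or rank sum | Paired t test |
| NPQ efficacy rate and adverse effects, as categorical variables | none | Chi-squared or Fisher |

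The first two rows each hold two rules with no order of precedence. The third is untouched by the gate.

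**3. Do the branches test the same thing?** With two groups, Tukey's studentized range statistic is √2·|t|, so the test is the pooled t test with null μ₁ = μ₂. The rank sum test has null F₁ = F₂ and responds to any departure of P(X<Y) + ½P(X=Y) from ½. Simulated rejection rates at 160 per arm with **equal means and different shapes** (the document gives no SD or shape, so these distributions are assumptions):

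| Arms | t test | Rank sum |
|---|---|---|
| Gamma, mean 12, shapes 4 v 2 | 0.051 | 0.229 |
| Gamma, mean 12, shapes 2 v 1 | 0.048 | 0.401 |
| Gamma, mean 12, shapes 4 v 1 | 0.059 | 0.798 |
| Normal v gamma (shape 1.5), same mean and SD | 0.054 | 0.185 |

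The gamma rows used 3,000 runs each and the last row 5,000. A gamma SD is mean/√shape, so 4 v 1 means SD 12/√4 = 6 against 12/√1 = 12. This is a large contrast, and the 0.798 is the far end of the range.

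**4. How often would the two tests disagree at 0.05?**

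| Scenario | t test | Rank sum | Different verdicts | Either significant |
|---|---|---|---|---|
| Identical arms, normal | 0.051 | 0.052 | 0.020 | 0.061 |
| Identical arms, gamma 1.5 | 0.048 | 0.050 | 0.040 | 0.069 |
| Identical arms, lognormal | 0.045 | 0.049 | 0.059 | 0.076 |
| Normal, shift 0.3 SD | 0.765 | 0.750 | 0.059 | 0.787 |
| Gamma 1.5, scale ×1.25 | 0.674 | 0.580 | 0.155 | 0.705 |

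Identical-arm rows used 20,000 runs, the others 5,000. The last column is the error rate only if the better of the two p-values is kept.

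**5. What does a gate do when it cannot see the effect?** With identical arms, a mechanical rule sent the data to the rank sum test when pooled skewness passed a cut-off (0 to 3) and otherwise to the t test (10,000 runs). Rejection was 0.050–0.051 (normal), 0.045–0.047 (gamma 1.2), 0.051–0.052 (gamma 4) and 0.048–0.051 (lognormal). A separate check with the skewness rule applied pooled or by arm gave 0.044–0.050. The gate alone does not inflate the error rate in these settings.

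**The case against.** The strongest reply is that little turns on the gate. The binary efficacy rate that sizes the trial goes to chi-squared or Fisher, and repeated measures ANOVA is already named for the repeated scores. The analysts are blinded, and a gate blind to the effect leaves type I error at about 5% when the arms are identical. The higher rank sum rejections in step 3 are not false positives under no difference, because those arms were built to differ. A numerical criterion for normality is also the kind of detail that an analysis plan may supply. All of this stands, and the absence of a cut-off is not the point made here.

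Some stronger readings are tempting but unsupported:

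- **Every outcome is decided by histogram.** Categorical outcomes are not, and homogeneity also enters the choice.
- **The type I error is not 0.05.** That needs an analyst who runs both tests and keeps the better one, which the text does not permit.
- **Scores will bunch at the floor because 85–95% succeed.** Success is only a fall of more than 30%: 50 to 34 on the NPQ is a 32% fall and is far from zero.
- **There will be 44 visual decisions** (11 scores at 4 post-baseline visits). No section prescribes a gated test per score and visit.

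What the reply does not remove is the conflict. Blinding to labels does not settle which analysis governs. A between-group test needs the data split by coded arm, and a two-sided p-value is the same whichever arm is tuina. Nor does it rescue the rank sum test for paired data.

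**Conclusion.** The point holds for the continuous scores. The section states a data-dependent choice between tests of different hypotheses, places it beside unconditional mean-based analyses of the same data, and gives no precedence. It also extends an independent-samples test to paired comparisons.

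Under the assumed shapes, the rank sum test rejects in 18.5–80% of trials with equal means, where the t test stays at 5–6%. The two verdicts differ in about 2–6% of trials with identical arms and 6–15% under the two assumed alternatives. The direction is secure; the sizes depend on distributions that the document does not give.

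An inflated type I error is not shown: about 0.05 with a blinded gate, and 0.06–0.08 as an upper bound if the better p-value is kept. The NPQ efficacy rate, 320 and 356 are unaffected. It is a defect of specification that should be corrected before database lock; it does not undermine the design.

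**What to change.** In Statistical analyses:

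1. Delete the histogram and homogeneity gate.
2. State in advance that NPQ change, VAS, NDI and each SF-36 domain are compared between arms by one mean-based longitudinal analysis, whatever the distribution looks like. This is the repeated measures model already named, with unequal-variance or robust standard errors and a 95% confidence interval for the difference.
3. Keep the rank sum test as a labelled between-group sensitivity analysis.
4. Drop Tukey for the two-arm comparison, where it only repeats the t test. That argument does not cover comparisons among five time points within a group; there the reason for one rule is that the paired test is already named.
5. For within-group change from baseline, keep only the paired test.

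The cost is a few sentences before database lock, with no change to sample size or data collection. A mean comparison can be slightly less efficient than a rank test if scores are heavily skewed. This depends on the shape: in the assumed gamma scale alternative, the t test had the higher power (67% v 58%). At about 160 per arm the t test held 4.5–5.1% under the identical-arm distributions in step 4, so the gate protects against little.

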**Methods/design:**

This is a multicenter, assessor- and analyst-blinded, randomized controlled trial with two parallel arms: a *tuina* group and a traditional Chinese massage group. A total of 356 eligible CNP patients will be randomly assigned to the groups in a 1:1 ratio. The intervention in the *tuina* group includes both structural and relaxation massage, while the traditional Chinese massage group will receive relaxation massage only. The interventions for both groups will last for 15 min and will be carried out three times a week for a period of 4 weeks. The primary outcome will be changes in the Northwick Park Neck Pain Questionnaire. Secondary outcomes will be measured by a visual analogue scale (VAS), the Neck Disability Index (NDI), and the 36-item Short-Form Health Survey (SF-36). The data will be analyzed at the baseline, at the end of the intervention, and during the 3 months of follow-up by repeated measures analysis of variance. The significance level is 5%. The safety of *tuina* and traditional Chinese massage will be evaluated after each treatment session. The results of this trial will help clarify the value of *tuina* and traditional Chinese massage as treatments for CNP and will highlight any differences in the efficacy of the treatments.

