**Fig. 2 Fig2:**
[figure not shown]
Study schedule showing time points for enrollment and assessment. NDI Neck Disability Index, NPQ Northwick Park Neck Pain Questionnaire, SF-36 36-item Short-Form Health Survey, VAS visual analogue scale, W-1 screening before enrollment, W0 baseline assessment, W2 assessment after the sixth treatment, which is in the second week, W4 assessment after the 12th treatment, which is in the fourth week, W10 assessment 10 weeks after the first treatment, W16 assessment 16 weeks after the first treatment

The main treatment center will be Yueyang Hospital of Integrated Traditional Chinese and Western Medicine affiliated with Shanghai University of Traditional Chinese Medicine, which will enroll 116 participants. Three other treatments centers—Sixth Hospital of Shanghai, Shuguang Hospital affiliated with Shanghai University of Traditional Chinese Medicine, and Jiading District Hospital of Traditional Chinese Medicine—will each enroll 80 participants.

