### Interventions

Participants will receive 12 sessions of treatment over a period of 4 weeks. Treatment will be performed by a senior therapist who has studied acupuncture and massage and has held a practitioner’s license for more than 10 years. They must have received professional training in *tuina* and massage. They must pass a test to ensure consistency of study methods before participating in the trial. The participants will be asked to rest for 15 min before treatment. A constant room temperature of 23 to 25 °C will be maintained to ensure the patients are comfortable and relaxed during treatment. Subjects will be advised to lie in the prone position on the treatment couch. The interventions will be performed three times a week. Each session will last for 15 min. Neck function will be assessed at baseline as well as at 2, 4, 10, and 16 weeks after the baseline assessment.

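### For the continuous scores, baseline is an outcome level and is adjusted for only on apparent imbalance, which shrinks the treatment main effect to 4/5 and gives up precision

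*Protocol article*

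**What the plan says.** The Statistical analyses section states that "Efficacy is measured at five time points" and concludes that "a repeated measures analysis of variance will be used to investigate the effect of treatment, time, and interaction terms between treatment groups versus time". The Interventions section identifies the five: "Neck function will be assessed at baseline as well as at 2, 4, 10, and 16 weeks after the baseline assessment". The Outcome measurements section lists six occasions, the sixth being screening. The abstract confirms that baseline is inside the model: "The data will be analyzed at the baseline, at the end of the intervention, and during the 3 months of follow-up by repeated measures analysis".

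Baseline adjustment is conditional: "If an adjustment for possible baseline incomparability is needed, a covariance analysis will be performed". The article gives no criterion for when it is needed, and does not say whether the main effect, the interaction or a contrast at one visit decides.

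The primary outcome appears in two forms. The abstract says "The primary outcome will be changes in the Northwick Park Neck Pain Questionnaire". The Primary outcome measurement section counts a patient as a success above 30% improvement and says "The NPQ efficacy rate is the percentage of participants for whom treatment was successful". The sample size rests on that rate, 95% against 85%.

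**The concern.** Under the Randomization section, allocation is revealed only after baseline data are collected, so the arms cannot differ systematically at baseline. A treatment main effect averaged over five levels therefore mixes one level with no possible effect into four where an effect may exist, and the estimate is pulled towards zero.

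The interaction is the other term named. It can detect that the profiles differ, but it does not say which arm is better, when, or by how much.

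The adjustment rule adds a separate problem. In a randomised trial the main reason to adjust for baseline is its correlation with the later score, and that correlation exists whether or not the arms look alike. Adjusting only when imbalance is seen gives up that precision in the usual case and makes the reported model depend on a look at the data.

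At stake are the size of the reported benefit and the efficiency of the analyses of the raw scores. The false positive rate of the ANOVA itself is not in question.

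**Working it through.** **1. The plan's own figure.** Inputs from the Sample size calculation section: 0.95 and 0.85, alpha 0.05, power 0.80, dropout 10%. Sidedness is not stated there; two-sided reproduces the figure.

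- Pooled formula: n = [1.96·√(2·0.9·0.1) + 0.8416·√(0.0475 + 0.1275)]² / 0.1² = 140.1 per arm.
- Continuity correction: (140.1/4)·[1 + √(1 + 4/(140.1·0.1))]² = 159.5, so 160 per arm and 320 in all.
- Dropout: 320/0.9 = 355.6, so 356.

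The figure reproduces. It concerns two proportions and is unaffected by what follows.

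**2. Dilution of the main effect.** With no effect at baseline and a constant difference d at four later visits, the five-level mean difference is (0 + 4d)/5 = 0.8d. This needs no SD or correlation, only a constant post-baseline effect.

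**3. Power.** The article gives no SD, correlation or effect for the continuous scores, so these are assumptions: SD 1, compound symmetry with correlation ρ of 0.3, 0.5 or 0.7, constant d, 160 per arm, normal approximation for single contrasts. Variances per patient:

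- Five-level main effect: V5 = (1 + 4ρ)/5, effect 0.8d.
- Mean of four post-baseline visits, unadjusted: V4 = (1 + 3ρ)/4, effect d.
- The same mean adjusted for baseline: VA = V4 − ρ², effect d.
- Interaction: centred effects are −0.8d once and 0.2d four times, with sum of squares 0.8d². The noncentrality is (160/2)·0.8d²/(1 − ρ) = 64d²/(1 − ρ), on 4 and 4·318 = 1272 df.

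d is set so that the adjusted mean has 80% power: d = (1.96 + 0.8416)·√(2·VA/160).

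| ρ | V5 | V4 | VA | d (SD) | Adjusted mean | Unadjusted mean | Five-level main effect | Interaction, 4 df |
|---|---|---|---|---|---|---|---|---|
| 0.3 | 0.440 | 0.475 | 0.385 | 0.194 | 80% | 71% | 55% | 28% |
| 0.5 | 0.600 | 0.625 | 0.375 | 0.192 | 80% | 58% | 43% | 37% |
| 0.7 | 0.760 | 0.775 | 0.285 | 0.167 | 80% | 40% | 28% | 47% |

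Example, main effect at ρ = 0.5: 0.8·0.192/√(2·0.6/160) = 1.77, and Φ(1.77 − 1.96) = 0.43.

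To match the adjusted mean, the main effect needs (V5/0.64)/VA = 1.8, 2.5 or 4.2 times the patients.

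**4. Precision given up by not adjusting.** The share of the variance of the post-baseline mean removed by the baseline score is ρ²/V4: 0.09/0.475 = 19%, 0.25/0.625 = 40%, 0.49/0.775 = 63%.

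**5. Centre.** The Study design section sets 116 patients for one centre and says that the other three "will each enroll 80 participants". If centre explains a share ICC of the variance, leaving it out multiplies the variance by 1/(1 − ICC). For assumed ICCs of 0.01, 0.05 and 0.10, a power of 80% becomes 79.6, 78.0 and 75.7%. The mean difference is not diluted.

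**The case against.** Several points against a wider criticism stand.

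- **Only one term is diluted.** A reader might infer that the plan's treatment effect as a whole is too small. The plan also names the interaction, which tests differential change and is not diluted, and nothing makes the main effect decisive. The section also plans other between-group tests and 95% confidence intervals, so the interaction is not the only output.
- **The gain depends on the contrast chosen.** With an assumed 0.3 SD effect, 160 per arm and ρ = 0.4, a baseline-adjusted analysis of week 4 alone has 0.3/√(2·0.84/160) = 2.93, power 0.833. The five-level main effect has 0.24/√(2·0.52/160) = 2.98, power 0.845. At ρ = 0.7 the adjusted week 4 contrast has 0.964 and the interaction 0.957. The large gain in the table belongs to the average over four visits. The article does not name week 4, or any visit, as primary.
- **The responder rate is different.** Response has no informative value at baseline, so the dilution argument does not reach it. A chi-squared or Fisher test is planned for categorical variables.
- **Centre is a side issue.** A reader might blame the absent centre term as well. It causes no dilution and costs about 0.4 to 4 points. No stratification by centre is stated, and an article may leave model factors to a fuller document.

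Condensation does not answer the main point. The article positively states both a five-level ANOVA and a conditional adjustment rule; these are choices, not gaps.

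**Conclusion.** The point holds for the raw NPQ, VAS, NDI and SF-36 scores, as a fault of efficiency and prespecification that does not invalidate the trial. Under a constant post-baseline effect the main effect is 20% too small. Relative to a baseline-adjusted four-visit mean with 80% power, the loss is about 25 to 52 points for the main effect and 33 to 52 for the interaction over ρ from 0.3 to 0.7. These losses rest on assumed compound symmetry, a constant effect and those correlations.

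A reader might infer that the trial falls short of its stated 80% power. The documents do not support that: the 80% belongs to the comparison of 95% with 85%, and 320 and 356 stand.

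**What to change.** Change the analysis wording as follows.

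- Delete the conditional rule and always include the baseline score as a covariate.
- For the continuous scores, model weeks 2, 4, 10 and 16 only, with treatment, visit, treatment-by-visit, baseline and baseline-by-visit.
- Name one treatment contrast in advance, for example the average over the post-baseline visits or one chosen visit, and report it with its 95% confidence interval. If a single visit is chosen, the power gain may be small.
- Analyse the NPQ responder rate with a logistic model adjusted for baseline NPQ.
- A centre factor may be added; it is optional and minor.

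No new data are needed. The cost is an amendment before database lock. The Trial status section says recruitment is under way, and under the Quality control section changes go through the steering committee to the ethics committee.

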### Sample size calculation

The expected efficacy rate of the *tuina* group measured by the NPQ is 95%. According to the literature, the efficacy rate for traditional Chinese massage is 85%. The sample size was calculated with a significance level of 0.05 and power of 0.80. According to the calculation in SPSS, the required sample size was 320. With a maximum dropout tolerance of 10%, 356 patients are needed for the trial, with 178 for each group across the four centers.

